### Randomization

Participants will be randomized during visit 2. The randomization process will be started after 16 patients who passed the screening test are enrolled, and randomization will be carried out three times in total. The steps of the randomization will be overseen by an institution unrelated to this trial. Except for the therapist playing the music, anyone related to the trial (investigators, participants, and monitors) will be blinded to the type of music therapy being used, and the outcomes will be evaluated by the investigators, not the therapist. The first step of the randomization process will be to generate a random number to allocate the patient (SPSS software, SPSS Inc., Chicago, IL, USA). The institution in charge of randomization will label the patients as ‘A’ or ‘B’ and report to the trial center, who will randomize the patients accordingly and assign them to the following sessions. The ratio of the OMMT group and the CMT group is 1:1.

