### Setting

This trial is a single-center, double-blinded, parallel-group randomized controlled trial, which will be performed at the Hwa-byung Stress Clinic, Kyung Hee University Hospital in Gangdong, Seoul. Patients will be recruited through internet advertisements, newspaper advertisements, and official notices posted in the hospital. Patients recruited for the trial will be required to visit the investigational site and sign a written informed consent form. Patients who sign the consent form, who are diagnosed as having Hwa-byung by the Hwa-byung Structured Clinical Interview for DSM (SCID), and who satisfy the inclusion and exclusion criteria will be registered into the clinical trial. The registered patients will be asked to complete the STAI, the H-scale, the CES-D, the H-VAS, and the WHOQOL-BREF. Once 16 patients have been registered randomization will commence, with equal numbers allotted to the the OMMT group and the CMT group. This randomization process will be repeated three times, until 48 patients are divided equally between the two groups. For 4 weeks the patients will receive either OMMT or CMT in groups of eight patients. Patients will complete the H-VAS at sessions 1, 4 and 8 of the trial, and also after session 8 (in week 4). Salivary cortisol will be collected on the day before session 1, and at session 8., and will be collected twice, at 0800 and again at 1700 hours. The time between the screening tests to the end of the trial may vary depending on the patient schedule. From the first session to the last follow-up in week 8, it will take approximately 53 days to complete the study. Figure
1 is an overview of this proposed trial, and Figure
2 is an approximate visit schedule.

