### Interventions

#### Oriental medicine music therapy

The OMMT program entails eight sessions of 60 minutes each, conducted twice a week over a period of 4 weeks, and composed of five different levels of activity.

The first level is abdominal breathing for 5 minutes; patients breathe rhythmically to slow Korean folk rhythms called *Jinyangjo* played by *Daegum*, a kind of traditional Korean flute. The purpose during this portion of the session is to begin breathing control before the start of the therapy itself. Daegum has the quality of decreasing qi.

The second level involves vocalization and sound. Patients are asked to make the sounds of *Kung*, *Duk*, and *Dung*, which are traditional Korean methods of pronouncing rhythm, using their own voice. This portion of the therapy is conducted twice a week for four weeks in a total of eight sessions 10 minutes each.

The third level of treatment is the five-element rhythm therapy, which takes 10 minutes. Patients stimulate five acupuncture points (GB-20, GB-21, PC-6, ST-40, and GB-31) with maracas to the rhythm of music that has the Wood-qi element of the five elements of music. The objective of this portion is to circulate the blood and *qi* using Wood-*qi* music, which has active characteristics when stimulated.

The fourth level is 10 minutes of spreading music therapy, which lets patients play music themselves using *Janggu*, a traditional percussion instrument.

The fifth level is a 10-minute session of relieving music therapy, in which patients beat out a rhythm with wood blocks, which induces Wood-*qi*. This is performed to the rhythm of Wood-*qi* music, which stimulates the liver *qi*.

The last level is singing with abdominal breathing for 15 minutes. Patients make the sounds of ‘mo’ and ‘mi’, out of ‘ma’, ‘me’, ‘mi’, ‘mo’ and ‘mu’, which have *yin* characteristics

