#### Control music therapy

The control music therapy program is also carried out for 60 minutes twice a week for 4 weeks, to give a total of eight sessions. Sessions 1 to 4 involve the patients playing different types of traditional music. Each session consists of three or four different types of music and each has the characteristic of reducing *qi*, making people calm, and lightly stimulating the mind from calmness, heartbreaking sadness, and happiness. From session 1 to 4, the music will be different at each session. The music played in sessions 5 to 8 will be the same music played in the session 1 to 4, but the music will be different at each session.

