## Discussion

There is no gold standard of measurement for Hwa-byung. However, anxiety is one of the main symptoms of Hwa-byung, and is a symptom with measurable endpoints, which enables doctors to quantify the level. This is why the application of the STAI to measure the level of Hwa-byung was chosen as the primary endpoint.

This study will use listening to traditional music as the therapy for the control group. Traditional music therapy is not specifically a placebo therapy, as it has been reported that traditional music therapy shows effects for a diverse number of psychological disorders. However, there is no doubt that OMMT is different from the listening to traditional music. The OMMT is based on traditional Korean medicinal theories such as the *yin*/*yang* theory and meridian theory. OMMT does not involve the passive listening to music; patients actively move their body, play the instruments, and thereby release stress. Although similar elements of music will be used, the essence of the two therapies is very different.

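### The trial is labelled double-blind with participants blinded, but participants can tell from their own activity which therapy they receive, and they complete the primary outcome themselves

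*Protocol article*

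**What the plan says.** The label appears in the Abstract (Methods/design) and again under Setting: "This trial is a single-center, double-blinded, parallel-group randomized controlled trial". The Randomization section says who is covered. With the therapist as the only exception, "anyone related to the trial (investigators, participants, and monitors) will be blinded to the type of music therapy being used". The same section adds that investigators, not the therapist, evaluate outcomes. An outside institution labels patients A or B, and the labels go in a "report to the trial center, who will randomize the patients accordingly and assign them to the following sessions".

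The OMMT section lists vocalised rhythm sounds, tapping five acupuncture points with maracas, a drumming stage "which lets patients play music themselves using" the *Janggu*, beating wood blocks, and singing: "The last level is singing with abdominal breathing for 15 minutes". The Discussion draws the contrast itself: "OMMT does not involve the passive listening to music; patients actively move their body, play the instruments, and thereby release stress". It describes the control as listening to traditional music and calls the two therapies very different in essence. The Hypothesis section says the control has no physical component.

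The Control music therapy section reads differently: "Sessions 1 to 4 involve the patients playing different types of traditional music".

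The primary outcome is the change in STAI from visit 2 to visit 9. Under Setting, patients complete the STAI, H-scale, CES-D, H-VAS and WHOQOL-BREF.

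**The concern.** The blinding statement concerns the type of therapy, which is more than keeping participants unaware of the hypothesis. A participant who is drumming and singing knows that this is the therapy received. So does one who is listening. The feature under test, active participation, is the feature that reveals the arm.

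This matters most where the participant is also the assessor. On a self-completed anxiety scale, a belief about how helpful one's therapy should be can enter the score directly. Readers who see a double-blind label will discount that explanation for a difference in STAI, and the design gives them no ground to do so.

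**Working it through.** **Step 1. Can participants tell the arms apart?**

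| Feature | OMMT | Control |
|---|---|---|
| Instruments | Maracas, *Janggu*, wood blocks (OMMT section) | Listening (Discussion); patients playing music (Control music therapy) |
| Acupuncture-point tapping | Yes | Not described |
| Vocalising and singing | Yes, singing for 15 minutes per session | Not described |
| Physical component | Yes | None (Hypothesis) |
| Session length and number | 60 minutes, eight sessions | 60 minutes, eight sessions |

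Dose and contact time are matched; activity is not. Even if control patients literally play music, the tapping, vocalising and singing still distinguish the arms.

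**Step 2. Which outcomes does the stated safeguard protect?** The safeguard is evaluation by investigators rather than by the therapist. The secondary outcomes are salivary cortisol, H-scale, CES-D, H-VAS and WHOQOL-BREF. Patients complete four of these five, and also the STAI. For those five instruments the patient produces the score, so the choice of evaluator does not blind them. Cortisol is the only outcome that is not self-reported.

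**Step 3. The plan's own figure.** Inputs from Sample size: change 8.82, SD 10.385, two-sided 5%, power 80%. Dividing by the squared difference,

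n = 2 × (1.96 + 0.84)² × 10.385² / 8.82² = 1691.06 / 77.79 = 21.7, so 22 per arm.

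This reproduces the stated 22, which the plan raises to 24 for drop-out. Nothing here depends on blinding, so relabelling leaves the sample size as it is.

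**Step 4. Illustration of what is at stake.** The documents give no size for an expectation effect. Let b be an assumed between-arm shift in reported STAI, with no true effect, 24 per arm and SD 10.385:

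SE = 10.385 × √(2/24) = 3.00

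P(significant) = Φ(b/SE − 1.96) + Φ(−b/SE − 1.96)

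| Assumed b (STAI points) | b / 8.82 | P(significant) |
|---|---|---|
| 0 | 0% | 5.0% |
| 2 | 23% | 10.2% |
| 3 | 34% | 17.0% |
| 4 | 45% | 26.6% |

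The *t* distribution gives nearly the same results (10.0%, 16.5% and 25.7% for b = 2, 3 and 4). A larger sample would not remove such a shift. A shift in the other direction would hide a true effect by the same number of points.

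**The case against.** The strongest reply is that knowing one's activity is not knowing which therapy is under test, and that expectation bias depends on the latter. The control is active, contact time is equal, both arms are treated in groups of eight, and people with regular music therapy or similar training in the past year are excluded. What participants are told cannot be seen, because consent pages are not part of the text available. Neutral presentation may already be in place. This stands as far as it goes: neither the presence nor the direction of a bias is established. It does not rescue the statement as written, which claims blinding to the type of therapy. The article describes no masking of the hypothesis and acknowledges no limit on participant blinding.

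A reader might infer several stronger things that the documents do not support:

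- *That there is no protection against bias at all.* Blinding of investigators and monitors is not shown to fail, randomization is overseen by an unrelated institution, and the therapist does not evaluate outcomes.
- *That one leak of the A/B code would unblind the whole trial.* This is speculation. The center receives the labels and assigns patients to sessions, but the article does not say which staff do so.
- *That the hypothesis goes untested if control patients play.* The Control music therapy section mentions no instruments for patients, and the Randomization section has the therapist playing, so loose wording is plausible. If control patients did play, the contrast would differ from the one stated, but OMMT would still differ in tapping, vocalising and singing.

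**Conclusion.** The point holds for participants and for the outcomes they report. The article claims a design property that its own account of the interventions rules out, and nothing in it resolves the contradiction. It covers all 48 participants, the primary outcome and four of the five secondary measures. The conclusion rests on the interventions being delivered as described and on patients completing the scales themselves, as Setting states.

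The size of any resulting bias is unknown. The false-positive rates above depend entirely on the assumed shift and should not be read as estimates for this trial. The contradiction stands without them. The conflict over whether control patients play or listen is also real, and it leaves the comparator unclear in the section meant to define it.

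**What to change.** 1. In the Abstract, Setting and Randomization, remove the double-blind label and take participants out of the list of those blinded. State that participants and the therapist are not blinded.
2. Keep blinding only for roles where it can be maintained (investigators handling the data, monitors, the statistician), and say which staff at the center see the A/B labels and assign patients to sessions.
3. Instruct staff to present both therapies neutrally, with no indication of which is expected to do better.
4. State that a difference on the self-reported scales may include expectation effects, and that salivary cortisol is the only outcome that is not self-reported. Cortisol need not be promoted above the other secondary outcomes.
5. Reconcile the Control music therapy section with the Hypothesis and Discussion on what control patients do.

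Most of this is wording. It changes neither the sample size nor the planned tests, and it does not remove any bias; it limits what the result may claim. The downside is a less favourable design label. The trial is already recruiting under an ethics approval, so the staff instruction or any change to participant information may need approval and cannot reach those already treated.

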### Statistical method

The primary endpoint is the STAI. Efficacy analysis will be performed both as per protocol (PP; participants completed the trial without any protocol violation) and as intention to treat (ITT; all randomly assigned participants). The PP dataset will comprise all the patients who completed all the treatment sessions and questionnaires, while the ITT dataset will comprise patients who received at least one treatment session.

The independent *t*-test will be used to compare the changes in the STAI between visit 2 (baseline) and visit 9 between the OMMT group and the control group. Analysis of covariance (ANCOVA), using the baseline score as a covariate, will be used to analyze the mean change in the STAI, the H-scale, the CES-D, the H-VAS, and the WHOQOL-BREF, and in salivary cortisol levels between the two groups.

Other issues not included in this protocol will follow the Korean Food and Drug Agency Clinical Statistical Guidelines (Medicine 65625–13353, 2000. 12.29).

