### Outcomes

#### Primary outcome

The primary outcome of this study is the change in the STAI between visit 2 (before treatment and visit 9 (after all sessions are completed).

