### Sample size

The primary outcome in this trial is the change in STAI between the baseline (visit 2) and after treatment completion (visit 9). The hypothesis is: H0: δ = Δ1-Δ2 < 0 and H1: δ = Δ1-Δ2 ≥ 0, where Δ1 is change in STAI between baseline and visit 9 and the baseline in the OMMT group, and Δ2: is change in STAI between baseline and visit 9 in the control group.

The sample size was calculated based on a *qigong* study of heart disease
[12]. In this study, the participants were divided into two groups: the ‘*qigong*’ and ‘relaxing’ groups. After eight sessions, in the ‘*qigong*’ group, the mean change in STAI-1 was 8.82 and the standard deviation was 10.385, which is in accordance with a two-tailed, α error of 5% and power of 80% shown in the following equation.

(1)$$N=\frac{2{\left(1.96+0.84\right)}^{2}10.385^{2}}{=22}$$

Therefore, we will be randomly assigning 24 participants to each group, assuming a 10% drop-out rate.

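### The primary STAI change is given both an unadjusted t-test and a baseline-adjusted ANCOVA, on two analysis sets, and the plan does not say which result decides the trial.

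*Protocol article*

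**What the plan says.** The Primary outcome section defines a single endpoint: "The primary outcome of this study is the change in the STAI between visit 2" and visit 9.

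The Statistical method section then gives that endpoint two tests in consecutive sentences:

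- An independent t-test "will be used to compare the changes in the STAI between visit 2 (baseline) and visit 9" between the arms.
- A second model: "Analysis of covariance (ANCOVA), using the baseline score as a covariate, will be used to analyze the mean change in the STAI". The same sentence extends this model to the secondary outcomes. Baseline is the only covariate named.

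The section also says "Efficacy analysis will be performed both as per protocol" and as intention to treat. No test and no analysis set is called primary, supportive or sensitivity, and no rule covers disagreement.

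On allocation, Setting says "Once 16 patients have been registered randomization will commence, with equal numbers allotted" to the two arms, and "This randomization process will be repeated three times, until 48 patients are divided equally between the two groups". Randomization agrees: "randomization will be carried out three times in total". That is three waves of 16, each split 8:8.

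**The concern.** One endpoint, two tests and two analysis sets give four p-values. With 24 patients per arm the two tests can fall on opposite sides of 0.05, and the plan leaves open which would be believed.

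The choice also affects precision. A t-test on change fixes the coefficient of the baseline score at one. ANCOVA estimates that coefficient, so it corrects for chance baseline imbalance and normally has a smaller error variance. If the t-test decides, the headline result does not benefit from this.

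A smaller matter is that the design balances the arms within wave while both models leave wave out. Any difference between waves then stays in the residual.

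**Working it through.** **Inputs from the Sample size section:** difference 8.82, SD of change 10.385, two-sided 5% error, 80% power, 24 per arm.

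**Assumptions, because the article does not give these:** correlation r between baseline and visit 9 STAI of 0.3, 0.5 or 0.7; equal SDs at the two visits; between-wave SD of 0, 3 or 5 points.

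**1. The plan's own figure.** 2 × (1.96 + 0.84)² × 10.385² / 8.82² = 21.74, which rounds up to the stated 22 per group. This calculation uses the SD of change, so it is the sample size for the unadjusted t-test.

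**2. Precision.** With a common SD σ:

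- variance of change = 2σ²(1 − r)
- residual variance after adjustment for baseline = σ²(1 − r²)
- ratio = (1 − r²) / [2(1 − r)] = (1 + r)/2

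The simulation used 40,000 runs per scenario, three waves of 8 + 8 and, in this table, no wave effect.

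| | r = 0.3 | r = 0.5 | r = 0.7 |
|---|---|---|---|
| ANCOVA variance / t-test variance | 0.65 | 0.75 | 0.85 |
| ANCOVA residual SD, 10.385 × √ratio | 8.37 | 8.99 | 9.57 |
| n per arm for 80% power, 21.74 × ratio, rounded up | 15 | 17 | 19 |
| Simulated power, t-test | 82.2% | 82.2% | 82.0% |
| Simulated power, ANCOVA | 94.2% | 90.8% | 87.0% |
| Opposite verdicts at a difference of 8.82 | 13.9% | 11.6% | 8.7% |
| Opposite verdicts under the null | 5.6% | 4.7% | 3.7% |
| Type I error if either test may be claimed | 7.8% | 7.3% | 6.8% |

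Each test taken alone keeps its type I error at about 5%. The noncentral t distribution gives 82.1% for the t-test at 24 per arm, in line with the simulation. A separate simulation of 8,000 runs gave 8.1%, 7.3% and 6.6% for the last row, hence about 6.5–8%.

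**3. Wave.** A wave effect common to both arms was added to the visit 9 score. Because each wave is split 8:8, it cancels from the difference between arms but remains in the residual when wave is left out.

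| ANCOVA, between-wave SD 5 | r = 0.3 | r = 0.5 | r = 0.7 |
|---|---|---|---|
| Type I error without wave | 3.3% | 3.5% | 3.7% |
| Type I error with wave | 5.2% | 5.0% | 5.1% |
| Power without wave | 90.3% | 86.7% | 82.7% |
| Power with wave | 94.1% | 90.7% | 87.0% |

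At a between-wave SD of 3, type I error without wave is 4.2% to 4.5%. With no wave effect, adding wave costs almost nothing: power is 94.1%, 90.8% and 86.9%, against 94.2%, 90.8% and 87.0% without it.

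**4. Degrees of freedom at 48 patients.** The t-test has 48 − 2 = 46. ANCOVA with baseline and wave has 48 − 2 − 1 − 2 = 43.

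**The case against.** The strongest reply is that a ranking can be inferred. The t-test is listed first and is applied to the primary outcome only. The sample size rests on the SD of change, which fits that test. The ANCOVA sentence takes in the STAI and all the secondary outcomes together. So the t-test may be meant as primary and the ANCOVA as supportive, and an analysis plan not shown here may say so. This is a fair reading, but the article does not state it. It gives the primary endpoint two analyses, which differs from leaving a detail to a later document. If the reading is right, the point about precision applies in full.

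It is also fair that a t-test on change is valid under randomisation, and that the baseline data are not wasted, since the ANCOVA is already planned. Listing the t-test first is not an error. What remains is that the more precise analysis should be the one that decides.

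A reader might infer three stronger things that the article does not support:

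- **That the trial will run at a type I error of 6.5–8%.** This would need a rule that success on either test counts, and no section says so.
- **That leaving out wave adds a p-value or inflates type I error.** It does neither. With an 8:8 split the standard error can only be too large on average, so the tests are conservative. A wave difference common to visits 2 and 9 also cancels from the change score, and the article gives no between-wave SD.
- **That the sample size is wrong for this reason.** The stated 22 per group reproduces for the t-test.

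**Conclusion.** The point holds. The plan does not settle which of two tests, on which of two analysis sets, decides the primary comparison.

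- **If the t-test decides,** power is about 82% where ANCOVA would give about 87–94%, and the t-test variance is 18% (1/0.85) to 54% (1/0.65) larger. These figures rest on assumed r of 0.7 to 0.3 and equal SDs.
- **If the choice stays open,** the two tests disagree in about 9–14% of trials at the design difference. Type I error reaches about 6.5–8% in the worst case.
- **Wave is the lesser part.** At an assumed between-wave SD of 5 points, leaving it out costs about four percentage points of ANCOVA power and makes the test conservative.

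This should be changed, but it does not invalidate the trial: each test is valid alone, and the stated sample size is unaffected.

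**What to change.** Replace the two sentences on the STAI with one primary analysis: ANCOVA of the visit 9 STAI score on arm, baseline STAI and randomisation wave (three levels), in the ITT set. Label the independent t-test and all per-protocol analyses as sensitivity analyses. Since the section describes the ITT set both as all randomised participants and as those with at least one treatment session, the same sentence should say which is meant.

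The cost is analysis wording and three degrees of freedom (46 to 43). Baseline STAI is already collected, and wave is known from the randomisation. The change should be made before unblinding.

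Do not add a therapy-group term as part of this change. Sessions run in groups of eight, so there are six groups, one per arm in each wave. A random group effect with arm and wave fixed would leave 6 − 1 − 1 − 2 = 2 degrees of freedom for arm (critical t 4.30). Even with zero group variance, power at 8.82 would be about 50%, 46% and 42% for r = 0.3, 0.5 and 0.7. Clustering by therapy group is a separate question with a real power cost, to be decided separately.
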